### Relevant Concomitant Care Permitted or Prohibited During the Trial

No restrictions will be imposed on the participants in either group during the study period. The participants will register treatments related to their MS, including rehabilitation treatments.

#### Provisions for Posttrial Care

All participants may continue to receive routine care from the MS outpatient clinic and multidisciplinary care, as needed. No other arrangements will be made for provision of posttrial care. All participants will be covered by the Norwegian Patient Injury law, providing entitlement to apply for compensation from the Norwegian System of Patient Injury Compensation in the case of any harm while participating in the study.

### Outcomes

#### Work Package 1 (RCT)

An overview of the selected valid and reliable outcome measures that will be used is outlined in Table 3. The primary outcomes will be the Multiple Sclerosis Work Difficulties Questionnaire-23 – Norwegian version (MSWDQ-23NV) scores and physical activity levels measured by ActiGraph wGT3x-BT monitors. We have chosen these primary outcomes as they cover the main parts of the intervention. The secondary outcomes cover factors associated with reduced employment and HRQoL, along with specific insights into gait capacity, balance, and trunk control.

All outcome measurements will be conducted at baseline and weeks 9, 16, and 52 to examine short- and long-term within- and between-group effects, as outlined in Table 4.

Two trained physiotherapists (research assistants), blinded to group allocation and not involved in the delivery of the intervention, will perform the assessments in the local hospitals near the municipalities where the participants live, and distribute the activity monitors. Questionnaires will be administered digitally through the Research Electronic Data Capture (REDCap) tool. The participants will provide information regarding the type and duration of MS, as well as their age, gender, smoking status, weight, social status, education, current work, employment status, well-being, and motivation for work and physical activity. The patients will also self-report MS attacks, physical activity (type, dose, frequency, intensity), medications, physiotherapy, and work-related meetings.

**Table 3 table3:** Outline of the primary and secondary outcome measures for WP^a^1.

Outcome and measures			Description

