**Methods:**

This prospective, single-blinded randomized controlled trial (RCT) will include 115 pwMS with Expanded Disability Status Scale (EDSS) scores of 0-4 randomly allocated to either a CoreDISTparticipation intervention group or usual care (control group). The CoreDISTparticipation intervention includes (1) information videos, hospital outpatient physiotherapist assessments, and meetings with employment consultants; (2) group-based physiotherapy in municipalities for 60 minutes over 6 weeks, one indoor CoreDIST balance session, one outdoor CoreDIST balance and high-intensity interval session, and tailored work follow-up; and (3) 6 weeks of digitally supported independent training, twice weekly. Assessments will be conducted at baseline, week 9, and week 16. Primary outcomes include Multiple Sclerosis Work Difficulties Questionnaire-23 – Norwegian version (MSWDQ-23NV) and ActiGraph wGT3x-BT monitor scores. Secondary outcomes include Trunk Impairment Scale – modified Norwegian Version (TIS-modNV), Mini Balance Evaluation Systems Test (MiniBESTest), AccuGait Optimized force platform, 6-minute walk test (6MWT), Multiple Sclerosis Walking Scale‐12, Multiple Sclerosis Impact Scale-29 – Norwegian version, EQ-5D-5L, and Fatigue Severity Scale – Norwegian version scores. The study will identify effects of CoreDISTparticipation versus usual care on work barriers, physical activity, balance, walking, fatigue, and quality of life, along with a health economic evaluation. Descriptive statistics and repeated measures mixed models will be performed using IBM SPSS version29.

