**Primary outcomes**			
	MSWDQ-23NV^b^	This measures how frequently individuals with MS^c^ perceive psychological/cognitive (11 items), physical (8 items), and external (4 items) barriers related to work, scored on a 5-point scale (0=best) [46].	
	Levels of physical activity measured using ActiGraph wGT3x-BT monitors	The monitors will be worn on a belt around the waist for 7 consecutive days. The average daily percentage of time in mild, moderate, and intensive physical activity and sedative time will be calculated [47].	

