### Sample Size

We calculated the sample size needed to detect a between-group difference, as observed in our pilot study [31], based on the MSWDQ-23NV scores. The mean score change from baseline to posttest was 5.9 for the intervention group and 2.3 for the control group [31]. Considering the observed SDs and covariances and calculating with a power of 0.8 and α=.05, the RCT will need to include 45 individuals in each group. Assuming a dropout rate of 20%, we decided to recruit 115 people with mild-to-moderate disability due to MS into the study.

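### Two unranked primary outcomes, but the full alpha of .05 and the 0.8 power are planned for MSWDQ-23NV alone, so neither figure carries over to the two-outcome claim

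*Protocol article*

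**What the plan says.** Outcomes, Work Package 1 (RCT), makes two outcomes primary, the "MSWDQ-23NV) scores and physical activity levels measured by ActiGraph wGT3x-BT monitors". The reason given is "We have chosen these primary outcomes as they cover the main parts of the intervention", which treats them as equals.

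Table 3 describes the second primary outcome as several quantities: "The average daily percentage of time in mild, moderate, and intensive physical activity and sedative time will be calculated". The Data Analysis section regroups the same monitor data as minutes of sedentary, light and moderate-to-vigorous time. No single activity variable is marked as the primary one.

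On visits, the Outcomes section states: "All outcome measurements will be conducted at baseline and weeks 9, 16, and 52 to examine short- and long-term within- and between-group effects". The abstract lists fewer: "Assessments will be conducted at baseline, week 9, and week 16".

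Sample Size rests on MSWDQ-23NV scores and the pilot's mean changes from baseline to posttest, 5.9 against 2.3. It concludes: "calculating with a power of 0.8 and α=.05, the RCT will need to include 45 individuals in each group". With 20% dropout allowed for, the target is 115. No power is given for the activity outcome.

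The statistical analysis section for Work Package 1 plans intention-to-treat mixed models, where appropriate, for between-group differences over the repeated measurements. It gives no rule for combining the two primaries.

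**The concern.** A trial with two primary outcomes needs a rule that turns two results into one conclusion. The rule fixes the error rate of the primary claim and the power to reach it. The article gives the ingredients of a two-outcome trial and the sample size of a one-outcome trial. Under any symmetric rule for the two primaries, at least one of the printed figures, .05 or 0.8, fails to describe the primary claim or is not shown to.

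The headline conclusion depends on this. Without a rule fixed in advance, a positive result on activity alone and one on MSWDQ-23NV alone could each be reported as the primary finding at an unadjusted .05. Because the activity outcome consists of several quantities, the choice of category adds further freedom.

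**Working it through.** **Inputs from the article.** Two primary outcomes; four activity quantities in Table 3; follow-up at weeks 9, 16 and 52; α = .05; power 0.8; 45 per group; difference in mean change 5.9 − 2.3 = 3.6 points; 20% dropout; 115 randomised.

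**Assumptions.** Tests are two-sided (sidedness is not stated). The SD of change is not printed, so 45 cannot be reproduced independently and the SD is solved from it. All correlations are assumed.

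**1. The plan's own figures.** From n = 2(z₀.₉₇₅ + z₀.₈)²·SD²/δ², with n = 45 and δ = 3.6:
- SD = 3.6 / [√(2/45) × (1.960 + 0.842)] = 6.10, a standardised difference d = 3.6/6.10 = 0.59.
- With the t distribution, SD = 6.03 and d = 0.597.
- With a one-sided .05 the SD would be 6.87 and d = 0.52.
- Dropout: 90/0.8 = 112.5, so 113, or 57 per group = 114. Both are close to 115.

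The stated size is therefore coherent for MSWDQ-23NV alone on one contrast.

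**2. Either outcome suffices, each at .05, one test per outcome.**
- Independent outcomes: 1 − 0.95² = 0.0975.
- Correlation 0.5: 0.091.

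**3. Scenario in which any visit may also carry the claim.** This takes two outcomes at three visits as six separate tests at .05:
- Independent: 1 − 0.95⁶ = 0.265.
- Simulated (500,000 draws): 23.5% with visit correlation 0.5 and independent outcomes, falling to 17.5% with visit correlation 0.8 and outcome correlation 0.5.

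Letting single activity categories count as well would raise these figures by an amount that depends on how the categories correlate.

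**4. Both outcomes required, each at .05.** Error is held at .05 or below. Joint power cannot exceed the smaller of the two powers, so at 45 per group it is at most 0.80. With independent outcomes:
- Activity power 0.80: 0.80 × 0.80 = 0.64.
- Activity power 0.50: 0.80 × 0.50 = 0.40.
- For joint power 0.80 with equal effect sizes, each test needs power √0.8 = 0.894, about 60 per group.

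**5. Alpha split to .025 each.** Power = Φ(d√(n/2) − z₀.₉₈₇₅), with z₀.₉₈₇₅ = 2.241:

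| Analysed per group | d√(n/2) | Power at .025 |
|---|---|---|
| 45 | 2.80 | 0.71 |
| 46 (115 with 20% lost) | 2.83 | 0.72 |
| 57 (nearly all of 115) | 3.15 | 0.82 |

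The sample size for 0.80 is multiplied by [(2.241 + 0.842)/(1.960 + 0.842)]² = 1.21, whatever the SD: 45 × 1.21 = 54.5, so 55 per group, 110 analysed and 138 recruited.

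**6. Activity outcome.** At two-sided .05, 45 per group gives 80% power for a difference of about 0.60 SD (the t-based d in step 1). The article does not say whether an effect of that size is expected.

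**The case against.** Four points can be made for the plan.

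- **Detail left to another document.** An SAP or the full protocol may hold the primary visit, the model contrast and the named activity variable. This stands: a reader might take the lack of a primary visit as a fault in itself, but the article does not support that. What remains is what the article itself fixes, namely two equal primaries beside a calculation that uses all of alpha on one.
- **Measured is not tested.** A reader might infer that each outcome is tested separately at all three visits and that any success counts. The article says only that outcomes are measured then, and it plans mixed models over the repeated measurements. One overall test per outcome would remove the visit multiplicity. This stands: the 17.5% to 23.5% in step 3 is a scenario and does not follow from the plan. The 9% to 10% for two outcomes would remain if either suffices.
- **Sample Size claims nothing for activity.** It says openly that it is based on MSWDQ-23NV. A reader might infer that the .05 and 0.8 are wrong for that outcome. They are not: both can hold for MSWDQ-23NV on one contrast. The difficulty is only that the Outcomes section makes a second outcome equally primary.
- **Power loss depends on attrition.** With nearly all 115 analysed, an alpha split still leaves about 0.82. This stands, but the plan itself assumes 20% dropout, and then power is 0.71 to 0.72.

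**Conclusion.** The concern holds in limited form. The stated .05 and 0.8 describe MSWDQ-23NV alone and do not extend to a claim on two unranked primaries. What fails depends on the rule that the article does not give:

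- Either outcome suffices: false-claim rate about 9% to 10%, and higher if single visits or activity categories may each carry the claim.
- Both required: error is held, but 0.80 is only an upper bound on joint power at 45 per group.
- Alpha split: MSWDQ-23NV power falls from 0.80 to about 0.71 at 45 per group.

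The power figures rest on two-sided tests and a back-solved SD. The 1.21 ratio in required size does not depend on the SD. An ordered rule with MSWDQ-23NV first would keep both printed figures valid for that outcome.

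**What to change.** Before outcomes are examined by arm, state the decision rule for the two primaries. One workable rule:

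1. Test the MSWDQ-23NV total score at two-sided .05 on one pre-named contrast.
2. Only if that is significant, test one named activity variable at two-sided .05.
3. Treat the other visits and activity categories as secondary.

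Choose the named visit by reference to what the pilot's posttest corresponds to. Sample Size ties it to no trial week, so the calculation cannot be assumed to apply to week 16 or to any other particular visit. Holm's procedure, or requiring both outcomes, is also acceptable if power is restated. Ranking MSWDQ-23NV first is a choice; its advantage is that it matches the existing calculation.

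In Sample Size, add that the 0.8 power applies to MSWDQ-23NV only and that 45 per group gives 80% power for an activity difference of about 0.60 SD.

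Timing matters. The Results section reports the 15-week retests complete in December 2024 and expects data collection to end in September 2025. Whether results by arm have been seen cannot be told from the article. If they have, report the rule as post hoc and show multiplicity-adjusted p-values.

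The cost is wording in the protocol and SAP and, where needed, a registry update, with no extra patients. The drawback of the ordered rule is that no confirmatory activity claim is possible if MSWDQ-23NV fails.

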**Primary outcomes**			
	MSWDQ-23NV^b^	This measures how frequently individuals with MS^c^ perceive psychological/cognitive (11 items), physical (8 items), and external (4 items) barriers related to work, scored on a 5-point scale (0=best) [46].	
	Levels of physical activity measured using ActiGraph wGT3x-BT monitors	The monitors will be worn on a belt around the waist for 7 consecutive days. The average daily percentage of time in mild, moderate, and intensive physical activity and sedative time will be calculated [47].	
**Secondary outcomes**			
	6MWT^d^	This measures the distance in meters walked within 6 minutes [48].	
	ActiGraph wGT3x-BT monitor	This counts the average number of steps taken per day.	
	EQ-5D-5L + complementary questions	This is the self-perceived HRQoL^e^ in five domains and a Visual Analogue Scale (score 0-100) on overall health [49]. Complementary questions will be asked on sleep, well-being, emotions, and social relations (advocated by the Norwegian Health Institute). A higher score indicates better self-perceived health.	
	Fatigue Severity Scale - Norwegian version	This is a self-report, 9-item scale that measures the physical, social, and cognitive effects of fatigue (score 1-7). A higher score indicates higher levels of fatigue [50].	
	Multiple Sclerosis Walking Scale-12	This 12-item scale measures the self-reported perception of walking, scored on a 5-point scale. A higher score indicates a higher impact of MS on the individual’s walking ability [51].	
	MiniBESTest^f^	This test involves pro-and reactive balance, dual tasks, and involving sit-to-stand, standing, and walking tests. There are 14 items scored on a 3-point scale. A higher score indicates better performance [52].	
	TIS-modNV^g^	Trunk control in sitting: This 6 item scale is scored on a 2- or 3-point scale (sum range 0-16 points). A higher score indicates better trunk control [53].	
	AccuGait Optimized force platform	This measures postural control in standing and one-leg standing: Balance in a quiet stance is expressed through the COP^h^ migration and amplitude of postural sway [54].	
	Multiple Sclerosis Impact Scale-29 – Norwegian version	This measures the self-perceived physical (13 items) and psychological (9 items) impact on HRQoL using a 5-point scale. A higher score indicates an increased impact of MS on the individual’s day-to-day life [55].	
	Patient Global Impression of Change (PGIC) – physical activity and balance	This global index is used to rate the response of a condition to a therapy (transition scale). Higher scores indicate self-perceived improvement [56].	

^a^WP: work package.

^b^MSWDQ-23NV: Multiple Sclerosis Work Difficulties Questionnaire-23 – Norwegian version.

^c^MS: multiple sclerosis.

^d^6MWT: 6-minute walk test.

^e^HRQoL: health-related quality of life.

^f^MiniBESTest: Mini Balance Evaluation Systems Test.

^g^TIS-modNV: Trunk Impairment Scale – modified Norwegian version.

^h^COP: center of pressure.

**Table 4 table4:** Overview of registrations and assessments.

Registration and assessment	Baseline	Weekly	Week 9	Weekly	Week 16	Monthly	Week 52
Standardized outcome measures	X^a^	—^b^	X	—	X	—	X
Physiotherapy and work-related meetings (baseline and week 52: report the last 3 months)	X	—	X	—	X	—	X
Current work, employment status, well-being	X	—	X	—	X	—	X
Self-reports: MS^c^ attacks, physical activity, medications physiotherapy, general practitioner, NAV^d^ consultations	X	X	X	X	X	X	X

^a^X: applicable.

^b^Not applicable.

^c^MS: multiple sclerosis.

^d^NAV: Norwegian Labour and Welfare Administration.

#### Work Package 2 (Utility Study)

The outcomes for WP2 will be the net utility gain, employment status, and cost utility (Table 5). Data related to participation in work will be obtained cross-sectionally at baseline in WP1 and after week 52 through self-registration and linkage to the NAV register. The participants will provide information about the type and number of follow-ups and treatments from the physiotherapist, the general practitioner, the neurologist, and the NAV consultant in digital questionnaires distributed from REDCap. From the NAV registry, data will be obtained for the following variables: work status, sick leave, WAA and disability benefits, family-related leave (ie, maternity leave), pension, social aid, and unemployment benefits.

**Table 5 table5:** Outline of outcomes for WP^a^2.

Outcome	Description
Net utility gain: QALYs^b^	QALYs will be calculated for both groups using EQ-5D-5L scores from WP1.
Employment status	The status for and changes in employment will be calculated based on self-reports and registry data from NAV^c^. To enable calculation of long-term effects, we will gather data on the aforementioned variables 1 year after the intervention.
Cost utility	Data on treatment costs will be obtained from the tariffs and weights used in municipal and specialist health care.

^a^WP: work package.

^b^QALY: quality-adjusted life-year.

^c^NAV: Norwegian Labour and Welfare Administration.

### Sample Size

We calculated the sample size needed to detect a between-group difference, as observed in our pilot study [31], based on the MSWDQ-23NV scores. The mean score change from baseline to posttest was 5.9 for the intervention group and 2.3 for the control group [31]. Considering the observed SDs and covariances and calculating with a power of 0.8 and α=.05, the RCT will need to include 45 individuals in each group. Assuming a dropout rate of 20%, we decided to recruit 115 people with mild-to-moderate disability due to MS into the study.

### Recruitment

Participants were recruited from the neurological outpatient clinics in three hospitals in Norway. Based on the prevalence of pwMS and the prospects of being able to recruit sufficient participants to form groups, only municipalities with >4500 inhabitants (n=19) or smaller municipalities (n=3) near an outpatient clinic in a neighboring municipality were invited to participate. Based on patient lists from the participating outpatient clinics, all individuals in the selected municipalities who met the EDSS score criterium received an invitation to participate.

### Assignment of Interventions: Allocation

#### Sequence Generation

Digital randomization to CoreDISTparticipation (intervention group) or usual care (control group) in a 1:1 ratio using block sizes of 4 and 6 with a random variation between the two block sizes was performed. Randomization was stratified based on the participants’ region of residence (north or south) to optimize the establishment of exercise groups and avoid geographical bias. Randomization was performed using REDCap hosted by the Clinical Research Department, University Hospital North Norway, a secure web-based app designed to support data capture for research studies, providing (1) an intuitive interface for validated data entry, (2) audit trails for tracking data manipulation and export procedures, (3) automated export procedures for seamless data downloads to common statistical packages, and (4) procedures for importing data from external sources [57].

#### Concealment Mechanism

The allocation sequence was generated outside REDCap and uploaded to the REDCap database prior to enrollment of participants and was not visible to the members of the research group performing the randomization.

#### Implementation

The allocation sequence was generated by an administrative member of staff at the Research Department at the Northern Norway Regional Health Authority. This member of staff is otherwise not connected to the project and will not reveal the allocation sequence to any member of the research team. A member of the research group not involved in assessment or treatment of the participants or in the generation of the allocation sequence enrolled participants into the REDCap database upon screening them based on the inclusion and exclusion criteria and whether they provided informed consent. Following baseline measurements, digital randomization to the intervention or the control group was performed.

### Assignment of Interventions: Blinding

In line with many rehabilitation studies, this will be a single-blinded study. The outcome assessors will be blinded to group allocation. All participants have been instructed not to reveal their group allocation to the outcome assessor. Blinding of participants will not be possible as there is no control group intervention. No procedures for unblinding are planned as this is a single-blinded study.

### Data Collection and Management

#### Plans for Assessment and Collection of Outcomes

Demographic data on age, gender, height, weight, social status, education, medical history (including the type of MS, years since diagnosis, EDSS score and MS-related medications), work status, and physical activity will be collected from each participant digitally through Nettskjema’s online forms. All questionnaires will be distributed digitally from the REDCap database, and the participants will be notified via email. The clinical tests will be performed at the patients’ local or regional hospital. Two assessors will be trained in all tests to be performed, and training will include calibration of the two assessors. Scores from the clinical tests will be noted on a paper form prior to entry into the REDCap database.

#### Plans to Promote Participant Retention and Complete Follow-Up

All visits to the hospitals, municipality physiotherapists, and NAV consultants are free of charge, and travel costs will be reimbursed. Trial meetings with the participating physiotherapists and NAV consultants will be held before, during, and after the intervention to address questions. All questionnaires will be distributed digitally, thus allowing the participants to answer them in their own pace and to allow for breaks.

#### Data Management

Digital consent forms and demographic data collected via online forms will be stored securely at the project database at the Tjenester for Sensitive Data (Services for Sensitive Data; TSD). Data for primary and secondary outcome measures will be collected and managed using REDCap. All patient-reported outcome measures (PROMs) will be distributed digitally from REDCap, and responses will automatically be entered into the REDCap database. Point scores for the Trunk Impairment Scale – modified Norwegian Version (TIS-modNV), the Mini Balance Evaluation Systems Test (MiniBESTest), and the 6-minute walk test (6MWT) will be entered manually into the REDCap database. Paper score sheets for clinical tests will be stored in a locked cabinet. Deidentified data stored at the TSD and in the REDCap database will be exported securely into a secure server at the Nordland Hospital Trust prior to statistical analysis. All data will be coded with the participants’ study IDs. A list of participants containing both names and study IDs will be sent to NAV, and NAV will return the registry data for all participants with study IDs but without names. All files will be sent securely as password-encrypted files via email; passwords will be sent separately via text messages. The files will be stored at the Nordland Hospital Trust’s secure server for research data. The data management plan is stored in the Trial Master File.

